**Figure 1 F1:**
[figure not shown]
Flow diagram of randomisation and allocation to paired consultations method.

**Table 1 T1:** Potential configurations of paired consultations for randomisation

**Group**	**Configuration**	**Consultation 1 (by the research endocrinologist)**	**Consultation 2 (by the routine endocrinologists)**
Reference (50% of participants)	1	FTF	FTF
Telemedicine (50% of participants)	2.1	VC	FTF
	2.2	FTF	VC

FTF: Face-to-Face, VC: Videoconference.

A block randomisation with the block size of eight will be used to ensure balanced representation of the participants in each group. The randomised configuration will be provided by an independent biostatistician using SAS software. Opaque sealed envelopes with sequential numbers will be used for allocating the participants into the groups.

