### Study setting and participants

This study will be conducted in the outpatient diabetes clinic of the Princess Alexandra Hospital (PAH) which is a tertiary teaching hospital in Brisbane, Australia. People with diabetes who have an appointment with an endocrinologist as a new or review case for the purpose of improving management of their diabetic condition will be approached and invited for participation. Six endocrinologists who attend the clinic routinely will visit the patients as scheduled (these are referred to as ‘routine endocrinologists’ in this paper). Another endocrinologist (referred to as the ‘research endocrinologist’ in this paper) will be employed for the purpose of this research to undertake the additional consultation for each patient who consents to participate in the trial. The additional consultation will be conducted by the research endocrinologist prior to the original consultation for each patient. However, the participant patients will receive both their consultations on the same day in the same clinic session. The routine and research endocrinologists are all specialist doctors with the same qualifications and credentials (i.e. accredited by the Royal Australian College of Physicians).

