### Randomisation

Participants will be randomly allocated in a 1:1 ratio into one of two study groups (Telemedicine or Reference group). In the Telemedicine group the participants will receive a paired-consultation in which one of the consultations is via video (FTF-VC or VC-FTF), but in the Reference group both consultations will be face-to-face (FTF-FTF). Figure 1 outlines the randomisation and allocation process. The first consultation in each paired-consultation will be provided by the research endocrinologist, whereas the second consultation will be provided by one of the routine endocrinologists of the clinic. Since the order of VC vs. FTF consultations are also randomised, there will be three potential configurations for the paired consultations of each participant (Table 1). With such design, half of the video consultations will be conducted by the research endocrinologist, and the other half by the routine endocrinologists of the clinic.

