### Informed consent and recruitment

Eligible patients will be contacted by phone prior to their appointment to explain the project and seek verbal consent. Once checked-in to the clinic for their appointment, patients who have verbally consented will be given the participant information sheet, and written consent will be obtained. Each participant will be offered two movie vouchers (valued roughly US$ 30.00) as a compensation and appreciation for participating in this study. Non-consenting or excluded patients will receive their routine service at the clinic.

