### Outcome measures

The outcome measure of this study is the difference in level of agreement between the two groups. Agreement will be calculated for each group (Reference group: FTF-FTF; Telemedicine group: FTF-VC or VC-FTF) and compared. For the comparison between two consultations to be accurate, it is necessary that the endocrinologists be blinded to each other’s assessment and recommendations. Part of this information can be communicated by the patient, which is inevitable, however the research endocrinologist has been requested to refrain from giving information about the assessment and treatment plan to the patient during the first consultation. Since the research endocrinologist adds nothing to the patient chart (either in hard copy or electronic records), it will ensure that the endocrinologists will be blinded to each other’s opinion on each patient.

The primary outcome measure is the level of change in patient’s medications during the consultation. Based on its impact, medication change is divided into three categories: Major, Minor, and No change (Table 2). When more than one category is applicable to a participant, the highest impact will be regarded as the overall impact of the medication change.

**Table 2 T2:** The categories of the impact of medication change

**Medication**	**Change**	**Category**
Insulin	Initiation of insulin	Major
	Cessation of Insulin	Major
	Change in regimen (type, injection frequency)	Major
	Dose adjustment	Minor
	No change	No change
Other hypoglycaemic agents	Initiation of new drugs	Major
	Cessation of drugs	Major
	Dose adjustment	Minor
	No change	No change
Other medications (hypertension, lipids, etc.)	Initiation of new drugs	Major
	Cessation of drugs	Major
	Dose adjustment	Minor
	No change	No change

Secondary outcomes focus on performing the physical examination, detection of diabetes complications and patient satisfaction. For each video consultation, the endocrinologist will be asked about any technical problem or limitation during the video visit. This will assist in understanding the barriers of videoconferencing for consulting people with diabetes.

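### A single disclosed block size of eight lets staff who know it and track the sequence deduce up to one in five group allocations; varied, withheld block sizes would reduce this at almost no cost

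*Protocol article*

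**What the plan says.** The Randomisation section of the protocol article allocates participants 1:1 to Telemedicine or Reference. Within Telemedicine the order of the two modes is randomised as well: "Since the order of VC vs. FTF consultations are also randomised, there will be three potential configurations for the paired consultations of each participant". Below Table 1 it gives one block size: "A block randomisation with the block size of eight will be used to ensure balanced representation of the participants in each group". The list comes from outside the clinic, "The randomised configuration will be provided by an independent biostatistician using SAS software", and concealment rests on envelopes: "Opaque sealed envelopes with sequential numbers will be used for allocating the participants into the groups".

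Study setting and participants describes a single hospital outpatient clinic, and the article mentions no stratification. Under Informed consent and recruitment, patients are first approached by phone and consent verbally. At check-in, "patients who have verbally consented will be given the participant information sheet, and written consent will be obtained". The only blinding described, under Outcome measures, is between the doctors: "it is necessary that the endocrinologists be blinded to each other’s assessment and recommendations". Patient and staff can see whether a consultation is by video.

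**The concern.** Sealed, numbered envelopes hide the next card. They do not hide what the earlier cards imply. With a constant, known block size and one running sequence, the rest of a block is determined once four places in either group have been used.

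This matters only if someone who can foresee an allocation can also influence who receives it. Some room for that remains at check-in. Written consent is still to be obtained, several patients may be waiting, the exclusion of severely ill patients calls for judgement, and the nurse brings glucose readings and laboratory results up to date on arrival. The outcome is agreement between two doctors on the level of medication change. Both percentage agreement and weighted kappa can depend on the mix of patients, so a difference in case mix between groups could distort the comparison.

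**Working it through.** **Inputs.** From the Randomisation section: block size 8 and ratio 1:1. From Sample size: 160 participants, 80 per group. Assumptions: each block holds 4 Reference and 4 Telemedicine places (implied by the ratio, not stated); there is one running sequence; for the configuration-level figure, each block splits 4/2/2.

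The article gives no predictability figure to reproduce. Its numbers are consistent with each other: 160 / 8 = 20 complete blocks, giving 80 per group.

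**Step 1. Group allocations that are certain.** For a block of 2m with m per group, the expected number of places filled after one group is used up is 2m/(m + 1). With m = 4 this is 8/5 = 1.6 per block, a share of 1/(m + 1) = 20%. Over 20 blocks, 20 × 1.6 = 32 of 160.

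Listing all C(8,4) = 70 balanced blocks confirms this:

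| Certain places in block | Number of blocks |
|---|---|
| 1 | 40 |
| 2 | 20 |
| 3 | 8 |
| 4 | 2 |

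(40×1 + 20×2 + 8×3 + 2×4)/70 = 112/70 = 1.6. The last place of every block is always certain, so the share is never below 1/8 = 12.5%.

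**Step 2. Best guess over all places.** The expected number of correct guesses is m + (2^(2m)/C(2m,m) − 1)/2 = 4 + (256/70 − 1)/2 = 5.33 of 8, or 66.6%, against 50% with no information.

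**Step 3. Three configurations.** With 4/2/2 per block, exact recursion gives 48/35 = 1.37 certain places per block; 1.37/8 = 17.1%. The group-level figure is the more relevant one, because the trial compares groups.

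**Step 4. Varied block sizes.** These results come from a simulation of 400 trials of 160. To compare like with like, the observer is again fully informed, knowing the set of possible sizes and every past allocation.

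| Block sizes | Certain | Best guess correct |
|---|---|---|
| 8 only | 19.9% (exact 20%) | 66.8% (exact 66.6%) |
| 4, 8 | 7.4% | 68.0% |
| 4, 8, 12 | 2.8% | 66.0% |
| 8, 12, 16 | 1.7% | 63.9% |

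Varying the sizes removes most of the certainty but little of the guessing advantage.

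**The case against.** The strongest reply is that 20% describes an ideal observer. That person must know the block size, know where each block starts, and have tallied every earlier group. The article does not say who enrols, who opens envelopes or who keeps a tally, and an article may properly leave that to the full protocol. Disclosure in the article does not show that clinic staff knew the size, or that recruitment was still open when it appeared. This stands, and it makes 20% a ceiling.

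A tally also takes effort. In Table 1, configurations 1 and 2.2 both begin with a face-to-face visit to the research endocrinologist, so the first consultation does not separate Reference from half of Telemedicine. The second visits are spread over six routine endocrinologists and three clinics a week. Casual observation would therefore fall short. Someone coordinating the study could still manage it, because video visits use the telehealth studio and only Telemedicine patients receive the satisfaction questionnaire.

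Room to steer is narrow as well. Patients hold scheduled appointments and have agreed by phone, so steering would mean reordering them or dropping some at check-in. That is limited, but not nil.

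A reader might go further and infer that staff would send simple, no-change patients to known video places, raising Telemedicine agreement and favouring non-inferiority. If simple patients are assumed to agree 30 points more often than complex ones, in an even mix (15 points either side of the average), and half the certain places are steered, the shift is 20% × 50% × 15 × 2 groups = 3 points. If all are steered it is 6 points, against a 20-point margin. The documents support neither the gap nor the steering. Even the direction is open. Take the planning values under Sample size (25/50/25%, kappa 0.7) and assume a simple common-kappa model. Agreement, given that one doctor chooses no change, is then 0.7 + 0.3 × 0.25 = 77.5%. Overall it is 0.7 + 0.3 × (0.25² + 0.5² + 0.25²) = 81.25%. Under that model such patients agree slightly less often than average.

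**Conclusion.** The point holds as a weakness in concealment. With one disclosed block size, up to one in five group allocations (1.6 of 8; 17.1% by configuration if blocks are 4/2/2) could be deduced in advance by staff who know the size and track the sequence. The envelopes do not prevent this, and some scope for selection remains at check-in. The figure rests on 4:4 blocks, a single unstratified sequence and a fully informed observer.

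Three stronger readings are not supported:

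- **One allocation in five is in fact known to recruiters.** The documents do not show that anyone has the knowledge this needs.
- **The comparison is biased toward non-inferiority by a stated amount.** Neither direction nor size can be derived from the documents. Nor would case-mix imbalance go wholly unseen, because patient characteristics are collected and baseline data reported. Adjustment for measured factors might still not remove it reliably.
- **Varied blocks would leave nothing certain.** That is wrong for an observer who knows the set of sizes.

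This is a cheap improvement to concealment, and no bias has been shown.

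**What to change.** Have the independent biostatistician generate the list with block sizes varied at random among multiples of four, for example 8, 12 and 16. This keeps the 2:1:1 split over the three configurations in every complete block (4/2/2, 6/3/3, 8/4/4). Withhold the sizes from clinic and recruiting staff, and keep the envelopes as planned. Of the sets examined, 8/12/16 leaves the least certainty and the lowest guessing success; 4/8 is clearly weaker.

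The cost is re-running the SAS list. Recruitment may end partway through a block, so exact 80/80 balance is no longer assured. The group difference is at most half the last block, which is 8 participants for a block of 16.

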### Informed consent and recruitment

Eligible patients will be contacted by phone prior to their appointment to explain the project and seek verbal consent. Once checked-in to the clinic for their appointment, patients who have verbally consented will be given the participant information sheet, and written consent will be obtained. Each participant will be offered two movie vouchers (valued roughly US$ 30.00) as a compensation and appreciation for participating in this study. Non-consenting or excluded patients will receive their routine service at the clinic.

### Usual care

Princess Alexandra Hospital operates three diabetes clinics a week in the outpatient clinic building. New patients are allocated a 45-minute, and review patients usually a 30-minute time slot for consultation. Wherever possible, review patients are scheduled to see the same endocrinologist they saw for their previous appointment to ensure continuity of care.

Following arrival at the clinic, the patient is received by a diabetes nurse practitioner and initial assessments such as measuring weight and blood pressure are performed. The nurse also downloads the blood glucose readings from the patient’s glucometer and updates the patient charts with the latest lab results. The patient then visits the endocrinologist. At the conclusion of the consultation, the doctor writes the progress notes and any pharmacy scripts that are required, requests pathology test(s), refers the patient to another specialist or other health professional where indicated, or arranges for hospital admission if needed. The patient is then scheduled for another follow up outpatient appointment, or care is transferred back to the referring GP with a management plan.

### Intervention

All participants, both in the Telemedicine and Reference groups, will receive an additional consultation (consultation 1) by the research endocrinologist who is employed for this study. This endocrinologist is officially qualified and credentialled to visit and manage patients at the clinic. The additional consultation will always occur prior to the original consultation (consultation 2). For the participants in the Reference group, both consultations will be face-to-face: consultation 1 by the research endocrinologist and consultation 2 by one of the routine endocrinologists of the clinic. For the participants in Telemedicine group, one consultation will be face-to-face and the other one via videoconferencing. The format of the first and second consultations (FTF-VC, or VC-FTF) for the participants in this group will be determined in the randomisation process. The final recommendation for patient management will be provided by the routine endocrinologists at the end of second consultation.

To ensure that the integrity of usual patient care is maintained for the participants in the Telemedicine group who will have their second consultation via videoconferencing (Table 1: configuration 2.2), they will be able to meet the endocrinologist face-to-face immediately after video-consultation, if required by either the endocrinologist or the patient.

### Access to patient information in video consultations

To be able to isolate the effect of videoconferencing from other factors on the outcome of each consultation, we assume that doctors would have access to the same patient information as in a face-to-face consultation. Since the endocrinologist and the patients will be in the same building for both face-to-face and video consultations, it will be possible to provide the endocrinologists with the full records of the patients in hard copy during the videoconferencing as well as access to the electronic patient record via the Queensland Health network. Similar to original consultations, the latest blood glucose readings will be downloaded from each patient’s glucometer and entered in the patient record by a practice nurse upon check-in of each patient to the clinic. That will ensure that the endocrinologists will have equivalent access to the latest blood glucose measures, in each of the paired consultations.

### Equipment and connectivity

Remote video consultation will be simulated using one video-enabled laptop dialling into the diabetes clinic telehealth studio. The telehealth studio is currently functioning and located in the same building of the clinic. For video consultations, the patient will be accompanied by a diabetes nurse educator, who will “host” the consultation and assist with aspects of clinical examination, if needed, under the direction of the endocrinologist. This arrangement closely emulates the typical situation for diabetes remote consultation by videoconference, where patients are accompanied either by a nurse or their GP.

The telehealth studio in the diabetes clinic, where the patient will sit, is equipped with a Tandberg codec 990MXP + camera unit, Sony Bravia 32” television, and an Audio-Technica microphone. This codec provides pan, tilt, zoom functions for the camera by both the local and remote parties. The endocrinologists will use a laptop with 13” screen and Cisco Telepresence Movi software ver. 4.2 (Cisco systems, San Jose, California, USA) to connect to the telehealth studio for conducting the video consultations. Both Tandberg codec and Cisco Movi are H.264 compliant and capable of high definition video (up to 1080p 30 fps) encoding and decoding. The laptop has been tested to be compatible with the Tandberg codec. This is the configuration that clinicians use when they provide remote consultations on a trip or in the facilities that dedicated VC equipment is not available. The connection will be through the existing Local Area Network (LAN) and Wireless LAN (WLAN) within the clinic building. Although the LAN bandwidth is 100 Mbps, the codec and software will be set on 384 Kbps. This bandwidth is generally regarded as the minimum connection speed for producing acceptable full screen, full motion video. Although the general connection speeds between the Queensland Health telehealth centres range from 512 kbit/s to 2.3 Mbit/s depending on site specific connections, selection of minimum required bandwidth will ensure the results of this research to be more generalizable to the countries that high speed networks are not readily available.

### Outcome measures

The outcome measure of this study is the difference in level of agreement between the two groups. Agreement will be calculated for each group (Reference group: FTF-FTF; Telemedicine group: FTF-VC or VC-FTF) and compared. For the comparison between two consultations to be accurate, it is necessary that the endocrinologists be blinded to each other’s assessment and recommendations. Part of this information can be communicated by the patient, which is inevitable, however the research endocrinologist has been requested to refrain from giving information about the assessment and treatment plan to the patient during the first consultation. Since the research endocrinologist adds nothing to the patient chart (either in hard copy or electronic records), it will ensure that the endocrinologists will be blinded to each other’s opinion on each patient.

The primary outcome measure is the level of change in patient’s medications during the consultation. Based on its impact, medication change is divided into three categories: Major, Minor, and No change (Table 2). When more than one category is applicable to a participant, the highest impact will be regarded as the overall impact of the medication change.

**Table 2 T2:** The categories of the impact of medication change

**Medication**	**Change**	**Category**
Insulin	Initiation of insulin	Major
	Cessation of Insulin	Major
	Change in regimen (type, injection frequency)	Major
	Dose adjustment	Minor
	No change	No change
Other hypoglycaemic agents	Initiation of new drugs	Major
	Cessation of drugs	Major
	Dose adjustment	Minor
	No change	No change
Other medications (hypertension, lipids, etc.)	Initiation of new drugs	Major
	Cessation of drugs	Major
	Dose adjustment	Minor
	No change	No change

Secondary outcomes focus on performing the physical examination, detection of diabetes complications and patient satisfaction. For each video consultation, the endocrinologist will be asked about any technical problem or limitation during the video visit. This will assist in understanding the barriers of videoconferencing for consulting people with diabetes.

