### Aims and objectives

In this study we are seeking to identify if telemedicine is a reliable vehicle for providing specialty consultation for people with diabetes using videoconferencing, with the implication that it would be useful to utilise when usual care is either not available or difficult to deliver. The aim of the study is to test the level of clinical agreement achieved using specialist to patient videoconferencing (VC) compared with face-to-face (FTF) consultation. To place this level of agreement in context, it will also establish the level of agreement among specialists using face-to-face consultation. This approach enables the variation in clinical decision making among clinicians to be identified, and thus to be differentiated from the effect of the VC mode of service delivery.

This study will test the hypothesis that the clinical assessment and recommendations as determined by an alteration in medication type or dose made by endocrinologists for people with diabetes via videoconference are significantly different from those made through face-to-face consultation (null hypothesis). Secondary hypotheses will apply the same analytic techniques to the other aspects of diabetes consultation: (i) ordering lab tests or other diagnostic intervention; (ii) initiation of new medication(s) or dose adjustment of the previously prescribed drugs for dyslipidaemia and/or hypertension; (iii) detection or management of diabetes related complications; and (iv) referring to other specialists or arranging hospital admission.

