### Statistical methods

Demographic and baseline data will be reported as absolute numbers, percentage, and/or mean +/− SD. Percentage agreement and the weighted kappa statistic (Kw) will be used to assess inter-rater reliability between the two groups on the agreement on assessments and recommendations made by the endocrinologists [21].

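### The primary agreement score compares only the size of the medication change, so paired recommendations that differ in drug class, type or direction can count as full agreement

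*Protocol article*

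**What the plan says.** The Aims and objectives section states the primary hypothesis for assessments and recommendations "as determined by an alteration in medication type or dose made by endocrinologists". The same section puts "initiation of new medication(s) or dose adjustment of the previously prescribed drugs for dyslipidaemia and/or hypertension" in secondary hypothesis (ii).

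The Outcome measures section turns the primary outcome into a three-level scale: "Based on its impact, medication change is divided into three categories: Major, Minor, and No change (Table 2". In Table 2, starting and stopping are both Major in all three drug groups (insulin, other hypoglycaemic agents, other medications). A change of insulin regimen is also Major. A dose adjustment is Minor whichever way it goes. Lipid and blood-pressure drugs are in the table. One value per consultation remains: "When more than one category is applicable to a participant, the highest impact will be regarded as the overall impact of the medication change".

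Under Statistical methods, "Percentage agreement and the weighted kappa statistic (Kw) will be used to assess inter-rater reliability". The Sample size section uses the same three levels.

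**The concern.** The hypothesis is about what the two doctors recommend. The score records only how large the change is. These pairs all count as full agreement:

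- one doctor raises a dose and the other lowers it (Minor-Minor);
- one stops insulin and the other changes its regimen (Major-Major);
- one starts a lipid drug and the other stops a hypoglycaemic agent (Major-Major).

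The third pair also matches a diabetes decision with one that the Aims treat as secondary. If video leads doctors to different actions of similar size, the primary outcome does not register it. The trial could then report that video is as reliable as face-to-face care although the recommendations differ.

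**Working it through.** **Inputs.** From the Sample size section: rates of 25% Major, 50% Minor and 25% No change, true kappa 0.7, null kappa 0.5, 80 per group, 5% significance, 80% power, margin 20%. The protocol gives no rates by drug or by direction of change.

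**The plan's own figure.** The 80 per group reproduces as a one-sided, one-sample test of a single unweighted kappa. The large-sample variances are the maximum over tables with these margins (0.5775 at kappa 0.5, 0.4017 at kappa 0.7): n = [(1.645 × √0.5775 + 0.842 × √0.4017) / 0.2]² = 79.5, rounded up to 80. The figure rests on the three levels and neither supports nor weakens this point.

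**Agreement that is never examined.** Assume the common-correlation model, in which P(both in category i) = p² + kappa × p(1 − p). At kappa 0.7:

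- Major-Major: 0.0625 + 0.7 × 0.1875 = 0.194
- Minor-Minor: 0.25 + 0.7 × 0.25 = 0.425
- No change in both: 0.194
- Total: 0.8125

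Major-Major plus Minor-Minor is 0.619, which is 0.619 / 0.8125 = 76% of all scored agreement. Only the No change pairs are certain to be the same recommendation.

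**Effect on the group difference when the category score shows none.** Let q be the share of Major-Major and Minor-Minor pairs in which both doctors recommend the same action. With kappa 0.7 in both groups, the action-level difference is 0.619 × (q in Reference − q in Telemedicine):

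| Gap in q (assumed) | Hidden difference, points |
|---|---|
| 0 | 0 |
| 0.1 | 6.2 |
| 0.2 | 12.4 |
| 0.3 | 18.6 |
| 0.4 | 24.7 |

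The 20-point margin is crossed at a gap of 0.20 / 0.619 = 0.32. A negative gap reverses the sign. If only Major pairs could differ in action, the hidden difference could not exceed 19.4 points.

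**Effect when q is equal but kappa differs.** Take kappa 0.7 in the Reference group and 0.5 in the Telemedicine group. At 0.5, Major-Major plus Minor-Minor is 0.15625 + 0.375 = 0.531, and No change in both is 0.156, so category agreement is 68.75%.

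- Category difference: 81.25 − 68.75 = 12.5 points
- Action level, q = 0.8: (0.8 × 0.619 + 0.194) − (0.8 × 0.531 + 0.156) = 10.75 points
- Action level, q = 0.6: 9.0 points

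Here the category score is slightly the stricter of the two.

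**The case against.** The impact scale is a deliberate choice. It is ordered, it suits weighted kappa, and the sample size is built on it. The outcome is a difference between groups, and the same coarse scale applies to both. The questionnaire (Additional file 1) is not shown and may record more detail.

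Two stronger readings are tempting, and the documents do not support them.

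- *One doctor starts insulin and the other stops it, and this scores as agreement.* This cannot happen. Both doctors see the same patient in one clinic session, the research endocrinologist writes nothing in the chart, and the final plan comes only at the end of the second consultation. The patient is either on insulin or not.
- *The score biases the trial towards non-inferiority.* That needs more within-category disagreement with video than face-to-face. It is plausible that video would act within categories as well as between them, but nothing in the protocol establishes it. With equal shares the category score is slightly stricter, as shown above.

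The objection therefore removes the claim of a known direction of bias and weakens the case for replacing the primary endpoint. It does not remove the mismatch. The scoring rule is fixed in the article itself, and whatever the questionnaire records, the stated primary outcome does not use drug class or direction.

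**Conclusion.** The concern holds as a limit on what the primary score can show. It measures agreement on the size of the change, whereas the hypothesis concerns type or dose. At the planning values about three quarters of the scored agreement (61.9 of 81.25 points) is never checked for content. The hidden difference between groups runs from 0 to over 20 points, depending on a gap in same-action share that the documents do not give. So the score is insensitive to one kind of harm from video, and non-inferiority could be declared despite it. The sizes rest on the common-correlation model with 25/50/25% rates and on assumed gaps in q. They are a range, not a forecast. Table 2 and the Aims also disagree on whether lipid and blood-pressure drugs belong to the primary or a secondary question.

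**What to change.** Keep the Major/Minor/No change score and pre-specify beside it an action-level agreement analysis by group. A pair agrees only if both doctors recommend the same type of change (start, stop, regimen change, dose up, dose down, none) in each Table 2 drug class. State how several changes within one class are compared. Report the group difference in percentage agreement against the same 20% margin, and do not conclude that recommendations are equally reliable on the category score alone. Confirm that the questionnaire captures dose direction. Reconcile Table 2 with the Aims on lipid and blood-pressure drugs.

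The cost in data handling is a recoding rule and perhaps one extra item. The statistical cost is lower agreement and less precision. With 80 per group and a 20-point margin:

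- 65% agreement in both groups (assumed): SE = √(2 × 0.65 × 0.35 / 80) = 0.0754, power about 76% at one-sided 2.5% or 84% at one-sided 5%;
- 81.25% agreement in both groups: SE = √(2 × 0.8125 × 0.1875 / 80) = 0.0617, power about 90% or 94%.

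Both levels are shown because the protocol does not say whether its 5% is one- or two-sided. The action code has no natural order, so weighted kappa stays with the category score. Matching by class still counts two different agents of one class as agreement, so this analysis narrows the gap without closing it.
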